## Abstract

**Background:**

Evidence shows that internet-based self-help interventions are effective in reducing symptoms for a wide range of mental disorders. To date, online interventions treating psychotic disorders have been scarce, even though psychosis is among the most burdensome disorders worldwide. Furthermore, the implementation of cognitive-behavioral therapy (CBT) for psychosis in routine health care is challenging. Internet-based interventions could narrow this treatment gap. Thus, a comprehensive CBT-based online self-help intervention for people with psychosis has been developed. The aim of this study is the evaluation of the feasibility and efficacy of the intervention compared with a waiting list control group.

**Methods:**

The intervention includes modules on delusion, voice hearing, social competence, mindfulness, and seven other domains. Participants are guided through the program by a personal moderator. Usage can be amended by an optional smartphone app. In this randomized controlled trial, participants are allocated to a waiting list or an intervention of eight weeks. Change in positive psychotic symptoms of both groups will be compared (primary outcome) and predictors of treatment effects will be assessed.

**Discussion:**

To our knowledge, this project is one of the first large-scale investigations of an internet-based intervention for people with psychosis. It may thus be a further step to broaden treatment options for people suffering from this disorder.

**Trial registration:**

NCT02974400 (clinicaltrials.gov), date of registration: November 28th 2016.

**Electronic supplementary material:**

The online version of this article (10.1186/s12888-018-1644-8) contains supplementary material, which is available to authorized users.

## Background

Schizophrenia and other psychotic disorders are severe mental disorders with heterogeneous symptom profiles encompassing positive symptoms such as persecutory delusions and auditory verbal hallucinations as well as negative symptoms such as social isolation and avolition [1]. In addition, they are accompanied by neuropsychological impairments in attention, memory, and executive functioning [2–6]. Sleep is impaired in the majority of people experiencing persecutory delusions [7] and levels of worrying are high [8, 9]. Besides symptoms, stigmatization is a major source of distress in people diagnosed with schizophrenia [10], even in the context of mental health care [11]. Lifetime prevalence of schizophrenia is about 1% and stable across different regions of the world and cultures [12]. Schizophrenia is accompanied by an enormous individual and societal burden [13, 14] and lies on position eight of the leading causes of disability-adjusted life years in 15- to 44-year-olds [15]. About 65% of individuals with a first episode relapse during the subsequent three years [16], resulting in inpatient costs about two to five times higher compared to non-relapsed patients [17].

As a complementary or alternative treatment option to antipsychotic medication [18], cognitive behavioral therapy for psychosis (CBTp) has emerged as an evidence-based treatment option for patients with schizophrenia and related disorders [19–24]. CBTp targets psychological mechanisms of symptom formation and maintenance that were primarily identified or corroborated using experimental psychopathology research [25–27]. The therapeutic framework and techniques of CBTp are to a large extent similar to those of cognitive behavioral therapy (CBT) for depressive or anxiety disorders (cognitive restructuring, reality testing, etc.). For example, the distress (consequence) related to hearing voices (situation) is assumed to be determined not by hearing voices per se, but predominantly by automatic thoughts and the according belief system. Consequently, alternative helpful beliefs about voices established with the help of cognitive techniques are supposed to result in less distress [28]. CBTp is likely to be effective for patients who choose not to take antipsychotic medication, too [29]. In regular mental health care, the effectiveness of CBTp has also been asserted [30], and neurocognitive deficits, comorbidity and poorer functioning pose no barrier to improvement during CBTp [28]. Consequently, national regulations such as the United Kingdom National Institute for Health and Care Excellence (NICE) guideline recommend that CBTp should be offered to every person with psychotic symptoms [31].

Acceptance and Commitment Therapy (ACT) focuses on noticing rather than changing thoughts and feelings [32]. ACT seems to be effective in treating mental health problems [33]. In schizophrenia, ACT helps people to cope with psychotic experiences using strategies such as cognitive distancing, which is characterized by learning to see one’s belief as a hypothetical statement rather than a fact. Instead of trying to change, modify, or control odd cognitions or disturbing sensory states, patients are encouraged to instead simply be aware of these experiences [34]. A meta-analysis showed a medium-sized effect of ACT on symptoms of psychosis [35].

The third type of treatment is the Metacognitive Training for psychosis (MCT), developed specifically for people with schizophrenia [36, 37]. MCT invites participants to critically evaluate cognitive biases such as jumping to conclusions and overconfidence in their thinking (metacognition). These biases might increase the likelihood of psychotic symptoms [38]. Studies show that MCT is efficacious in reducing psychotic symptoms [39, 40].

Despite the availability of evidence-based treatments for schizophrenia, 69% of patients remain untreated in countries with low and middle income [41]. In particular, the need for psychosocial treatments including CBTp remains unmet [42]. Even in highly developed countries such as the United Kingdom or Germany, the treatment gap for schizophrenia is large. In theory, the NICE guidelines proclaim that CBTp is mandatory for the treatment of psychosis [31]. In practice, more than 50% do not receive even a single session of CBTp [43]. In Germany, CBTp is virtually not represented in the mental health service [44]. To sum up, CBTp is effective, recommended, and has great potential to alleviate psychological distress, but only a small fraction of patients with psychosis receives CBTp.

Internet-based cognitive behavioral therapy (iCBT) can help to overcome treatment gaps in many mental disorders [45]. In several psychological disorders, including anxiety and depression, internet-based treatments have proven to be efficacious and effective in randomized controlled trials (RCTs; for a comprehensive review, see [46]). Most of the growing body of evidence comes from studies evaluating guided internet-based self-help treatments. While patients work their way through a structured self-help program that is typically based on CBT manuals, therapists or coaches assist and support them via a secured e-mail system. Meta-analyses on internet-based treatments show a superiority of guided interventions in comparison to unguided, automated programs in terms of efficacy, adherence to treatment, and drop-out rates [47–49]. Main advantages of guided internet-based treatments include: (1) low-threshold accessibility, (2) flexible usage independent of time and place at a self-determined pace, (3) high levels of anonymity and privacy (which is an attractive feature for many persons with a mental disorder due to their fear of stigmatization) and (4) low costs of delivery to large populations [50].

People diagnosed with schizophrenia use the internet [51] and are able and willing to use mental health services on the internet, such as peer-to-peer support [52]. The feasibility of internet-based treatments for people with psychosis (iCBTp) is well documented for web-based interventions [53, 54] and also reported for smartphone interventions [55]. However, current internet-based programs differ in their comprehensiveness and focus. For instance, mixed results have been reported regarding the efficacy of internet-based psychoeducation programs [56], and the efficiency of internet-based programs targeting medication management [53, 57]. There is a pilot study on a more comprehensive web-based, CBTp-oriented program for auditory verbal hallucinations, but this program was delivered via computers in mental health care centres (and not online). The study provided promising results using an uncontrolled pre-post-design (Cohen’s d = 0.58) [58]. None of the 21 participants with schizophrenia reported that the program was unhelpful and the authors report no adverse events, highlighting the feasibility of iCBTp in a computerized self-help format. A recent investigation of aforementioned program in an RCT design showed a comparable effect of the web-based intervention and usual care on levels of auditory hallucinations [59]. The study was able to show that patients with schizophrenia who used the web-based program, however, had increased significantly in social functioning and their knowledge about CBTp was larger than of those who did not use the program. In another study that investigated iCBT for people with schizophrenia, the web-based program specifically targeted comorbid depressive symptoms. The intervention lead to a significant decline in depression severity [60].

In summary, there is preliminary evidence that iCBTp for people diagnosed with schizophrenia could be beneficial. However, to the best of our knowledge, no larger trials on comprehensive treatments have been conducted. The overarching goal of this RCT is to evaluate a guided internet-based self-help intervention for people with psychosis. We developed a web-based program that is comprehensive in many respects: The program is not only based on CBT but also includes elements from its third wave, specifically ACT and MCT [34, 36]. Schizophrenia patients often have comorbidities, such as depression, which should be addressed in an appropriate treatment [61]. This program offers additional interventions for such comorbidities. Disrupted sleep and worrying, among other secondary symptoms, are crucial in the formation and maintenance of psychotic disorders [25]. These factors are considered in the intervention as well. According to a review, the effects of smartphone-enhanced self-help are promising [62]. The intervention therefore includes an accompanying smartphone app for access in symptom-relevant situations in daily life. The app is expected to facilitate a transfer of skills to real world settings. Finally, a specific goal of the intervention was not to overstate negative consequences of the disorder [63] and solely focus on deficits, but to specifically target resources of the participants [64].

Treatment adherence in schizophrenia has been a well discussed topic predominantly in medication treatment [65]. But also in psychological treatments, rather high dropout rates are reported (e.g. prematurely terminated treatments by 45% of patients) [66]. This led us to look for factors that might influence treatment adherence. Among others, suggested mediators are treatment motivation [67] and working alliance with the therapist [68]. Overall, the study tests whether a comprehensive internet-based self-help program with an accompanying smartphone app reduces symptomatology in people with schizophrenia.

## Methods

### Study design

The study is an RCT of parallel design comparing the efficacy of guided internet-based self-help treatment for patients with schizophrenia to a waiting list control group (Fig. 1). Participants in the control group receive access to treatment after the intervention period of eight weeks. The long-term effect of the intervention is measured by a follow-up assessment six months after the intervention period has ended and is not part of the RCT design.

**Fig. 1 Fig1:**
[figure not shown]
Participant flow

### Sample size

A power analysis with the software G*Power [69] resulted in a target sample size of 128 to detect a medium-sized effect (*f* = 0.25) with α = 0.05 and a power of 0.80 for an ANCOVA. Including an assumed attrition rate of about 10%, the final number of participants should reach 140.

### Recruitment

Participants will be recruited in three different ways: First, the study staff will contact former patients with diagnoses of schizophrenia who consented to get contacted and inquire whether they are interested in participating in this study via e-mail. Second, study information will be sent out to psychiatric institutions in Switzerland and Germany. The health staff at those institutions can then distribute the information to interested and suitable patients directly, for example those patients who leave the institution and look for a continuation treatment. Lastly, online bulletin boards and informative websites on psychoeducation specifically created for people affected by schizophrenia will be targeted for publishing descriptions and links to the study.

### Eligibility criteria

To be included, participants must fulfill all inclusion criteria and not show any exclusion criteria described below. Suffering from other psychiatric disorders such as depression or anxiety disorders (part of the former ‘axis I’ disorders) does not lead to exclusion as long as the schizophrenia spectrum disorder is the primary diagnosis.

Inclusion criteria are:An age of 18 years or older.Provision of electronic informed consent.Access to the internet.Command of the German language.Fulfilling the diagnostic criteria for either schizophrenia, delusional disorder or schizoaffective disorder in their lifetime according to the structured Mini International Neuropsychiatric Interview (MINI) [70] administered during a telephone interview. These diagnoses are allowed to be partly remitted.A score of three or higher on the items assessing delusions (P1), hallucinations (P3) or suspiciousness/persecution (P6) on the Positive and Negative Syndrome Scale (PANSS) [71] showing that some positive symptoms remain.Simultaneous treatment with antipsychotic medication (or regular psychological or psychiatric care in Germany).

Exclusion criteria are:Acute suicidality.Representing an acute danger for others.No agreement on compiling an emergency plan.Diagnosis of an acute neurological disease of the central nervous system that needs to be treated.

### Randomization

Participants eligible for inclusion will be randomly allocated to one of the two groups (intervention or waiting list control group). Randomization and allocation will be prepared in advance by an independent researcher. This researcher will remain blinded to all processes within the intervention. An automated, web-based randomization service (www.random.org) [72] will be used to generate the randomization list. The allocation ratio will be 1:1.

### Intervention

The intervention called *EviBaS* (for ***Evi****dence-****Ba****sed ****S****elf-help* intervention) consists of an online program based on CBT principles, while also including components of ACT and MCT treatments. A smartphone app provides the possibility of exercising the modules in everyday life. There are 11 text-based modules in the online program, addressing a variety of topics (see Table 1). Each module includes texts and a worksheet. The worksheets can also be accessed via the optional app. The only mandatory module is the introductory one. After completion, the participants can choose from the remaining ten modules freely. Relapse prevention is recommended as the last module. Study participants are asked to work on approximately one to two modules per week. The time required to finish one module may vary, but will usually not exceed 60 min. The intervention is self-paced, so that participants are able to work on topics they prioritize, such as emotional issues rather than positive symptomatology [73].

**Table 1 Tab1:** Modules of the online program EviBaS

Name	Description
Introduction	Reflect on thoughts, feelings and behavior to understand and decrease the symptom burden.
Feelings of Threat	Review the effects of paranoia on individual goals and needs.
Voice Hearing	Learn strategies to reduce distress caused by hearing voices (better coping, influence the evaluation of voices).
Self-Worth	Find forgotten strengths and train a balanced sense of self.
Overcoming Depression	Set up activities and scrutinize depressing thoughts.
Worrying	Minimize upholding factors of worry and tackle worries with problem solving skills.
Sleep	Discuss maintaining factors of the sleep disorder, such as sleep hindering thoughts or disadvantageous surrounding factors.
Mindfulness	Exercise to direct your attention on one thing without judgement.
Metacognition	Learn in interactive exercises to avoid jumping to conclusions and overconfidence in errors.
Social Competence	Plan and train three different types of social situations: enforcing interests, shaping relationships, and winning sympathies.
Relapse Prevention	Collect individual warning signs and plan ahead.

While working with the program, participants will be in contact with a personal moderator if they want to. The moderator will guide the participants through the program with at least one message per week. The main goal of this steady contact is to help participants structure their usage of the program and to encourage regular participation [47]. If necessary (in case of a participant not using the intervention for seven days), the moderator reminds the participant to interact with the program. Participants’ questions are answered within three workdays by moderators. There is a biweekly supervision of all the moderators in the study team led by a licenced psychotherapist with extensive experience in CBTp.

### Measures

The primary outcome is the reduction of psychotic symptoms (positive symptoms such as voice hearing and paranoid delusions) at post assessment (directly after the completion of the intervention). Secondary outcomes include the level of symptomatology at follow-up, the number of dropouts and the results of all secondary questionnaires which evaluate quality of life, depression severity, treatment satisfaction, the influence of treatment expectancy, and process measures, among others (see Table 2). Assessments will be completed at baseline, eight weeks and 32 weeks. For an overview of all primary and secondary outcome measures, predictors and moderators, as well as process measures, see Table 2.

**Table 2 Tab2:** An internet-based intervention for people with psychosis (EviBaS): Schedule of enrolment, intervention and assessments

	Study period				
	Enrolment	Allocation	Post-allocation		Close-out
Timepoint	t-1	t0	t1 intervention/waiting period	t2 post assessment	t3 follow-up assessment
Eligibility screen	X				
Informed consent	X				
Allocation		X			
Interventions:					
EviBaS intervention group			X		
Waiting list control group			X		
Assessments:					
Primary outcome measures					
Positive and Negative Syndrome Scale (PANSS)	X			X	X
Mini International Neuropsychiatric Interview (MINI)	X			X	X
Paranoia Checklist	X			X	X
Launay–Slade Hallucination Scale (LSHS-R)	X			X	X
Secondary outcome measures					
Delusion and Voices Self-Assessment (DV-SA)	X			X	X
Rosenberg Self-Esteem Scale (RSES)	X			X	X
Insomnia Severity Index (ISI)	X			X	X
Penn State Worry Questionnaire - Abbreviated (PSWQ-A)	X			X	X
Patient Health Questionnaire (PHQ-9)	X			X	X
Box Task	X			X	X
Mindful Attention Awareness Scale (MAAS)	X			X	X
Interpersonal Competence Questionnaire (ICQ; subscales initiation and negative assertion)	X			X	X
Incongruence questionnaire (K-INK)	X			X	X
World Health Organization Quality of Life Assessment (WHO-QoL-BREF)	X			X	X
Internalized Stigma of Mental Illness – short version (ISMI)	X			X	X
Predictors and moderators					
Medication Adherence Rating Scale (MARS-D)	X			X	X
Attitudes towards Psychological Online Interventions (APOI)	X				
Credibility/Expectancy Questionnaire (CEQ)	X				
University of Rhode Island Change Assessment (URICA)	X				
Client Satisfaction Questionnaire (CSQ)				X	
Questionnaire Side Effects Psychosis and Internet (QueSPI)				X	
Process measures					
Working Alliance Inventory – Short Revised (WAI-SR)		X			
Intermediate Assessments Questionnaire		X			

### Primary outcome measures

#### Positive and Negative Syndrome Scale (PANSS)

The PANSS [71] was the first standardized evaluation tool for symptoms of schizophrenia [74]. It assesses 30 symptoms, which can be grouped into five factors: positive symptoms, negative symptoms, disorganization, excitement, and emotional distress [1]. The positive symptom factor serves as the primary outcome of this study. It includes nine items (delusions, hallucinations, unusual thought content, suspiciousness, grandiosity, somatic concern, active social avoidance, lack of judgment and insight, and (less) difficulty in abstraction). In this study, clinicians administer the PANSS via telephone.

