#### MINI International Neuropsychiatric Interview (MINI)

The MINI is a diagnostic structured interview for the assessment of psychiatric diagnoses [70], with a corresponding German version [75]. The specificity of the MINI was reported as good for all diagnoses (ranging from 0.72 to 0.97) [70]. In this study, a part of the MINI (depressive episode, suicidality, manic episode, and psychosis) was also administered via telephone.

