#### Launay–Slade Hallucination Scale (LSHS-R)

The LSHS-R is the revised version of the LSHS, developed by Launay and Slade in 1981 [77]. It includes 12 items and measures the predisposition to hallucinations on a wide spectrum [78]. There is a German version of the LSHS-R, which shows a Cronbach’s alpha of .87 in a patient sample and therefore is comparable to the original [79]. The five-point Likert scale ranges from 0 (‘certainly does not apply to me’) to 4 (‘certainly applies to me’) and there is a sum score that will be compared between both groups of participants.

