### Statistical analyses

Based on the intention to treat sample, a linear mixed-model repeated measures ANOVA with time (T1-T2) as a within-group factor and study condition as a between-group factor will be used for the main research question. Mixed-model repeated measures ANOVA uses all available data of each subject and does not require the substitution of missing values. Sensitivity analysis will be conducted to analyze the impact of dropout on the results. The significance level is set at 5%. We are also interested in possible mediators and/or moderators of the relation between the internet-based self-help intervention and positive psychotic symptoms. We will therefore test whether predictors identified in the literature, such as treatment motivation, working alliance or usage of the intervention could mediate and/or moderate the main effect [119]. To evaluate these possible predictors of treatment outcome, we use change scores of outcome measures as the dependent variables.

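### The text names one primary outcome, the PANSS positive factor, but Table 2 and the section heading class four instruments as primary, and nothing says which decides the trial

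*Protocol article*

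**What the plan says.** The protocol article describes its primary outcome in three ways.

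- **By construct (Measures):** "The primary outcome is the reduction of psychotic symptoms (positive symptoms such as voice hearing and paranoid delusions) at post assessment". No instrument is named.
- **By a single score (PANSS subsection):** "The positive symptom factor serves as the primary outcome of this study". This factor has nine items and is rated by clinicians over the telephone.
- **By a list of instruments (Table 2 and the section heading):** under "Primary outcome measures" Table 2 places the PANSS, the MINI, the Paranoia Checklist and the LSHS-R. The Methods section with the same heading describes the same four, and a separate section on secondary outcomes then opens with the DV-SA. The Measures section treats the table as authoritative: "For an overview of all primary and secondary outcome measures, predictors and moderators, as well as process measures, see Table 2".

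For the LSHS-R the article adds that "there is a sum score that will be compared between both groups of participants". The Statistical analyses section specifies a mixed-model ANOVA for the main research question without naming the variable analysed, and states once that "The significance level is set at 5" per cent. The Sample size section covers one ANCOVA comparison.

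**The concern.** The primary outcome fixes what the trial may conclude, and here the article gives two incompatible answers. The grouping of four is not a slip in one table cell, because table and section structure agree. The construct definition does not settle it either: hallucinations and paranoid ideas are also what the LSHS-R and the Paranoia Checklist address.

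The choice matters because the four instruments differ in kind.

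- **PANSS:** rated by diagnostic staff who, under Ethical aspects and data safety, are blinded to allocation.
- **Paranoia Checklist and LSHS-R:** completed by participants, who know whether they received access at once or are waiting. The LSHS-R is also described as an instrument that "measures the predisposition to hallucinations on a wide spectrum", which is not plainly the same thing as current symptom severity.
- **MINI:** a diagnostic interview. The article says that "a part of the MINI (depressive episode, suicidality, manic episode, and psychosis) was also administered via telephone". Three of those four parts are not positive symptoms, and diagnoses do not fit a linear mixed-model ANOVA.

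If the blinded PANSS factor showed no difference and a self-rating did, the present text would allow the self-rating to be reported as a primary outcome measure. A later analysis plan could adopt either set and claim to follow the protocol.

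**Working it through.** **1. Which set does the sample size match?** Inputs from Sample size: f = 0.25, α = 0.05, power 0.80, target 128. For two equal groups d = 2f = 0.5.

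- Noncentral F, 1 numerator df and one covariate: λ = N·f² = 128 × 0.0625 = 8, error df = 128 − 2 − 1 = 125, power = 0.801. The smallest N reaching 0.80 is 128, as stated.
- Normal approximation: 2 × (1.960 + 0.842)² / 0.5² = 62.8, so 63 per arm and 126 in all, in agreement.
- The final figure of 140 is close to 128 × 1.1 = 140.8 and 128 / 0.9 = 142.2, and raises no issue here.

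The trial is therefore sized for one test at 5%, which fits the PANSS sentence and not the Table 2 list.

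**2. How many scores could the Table 2 list yield?** Leaving the MINI aside as categorical, one score per scale gives three: PANSS factor, Paranoia Checklist, LSHS-R. The Paranoia Checklist has three subscales (frequency, conviction, distress) and no total score is named. Counting them separately gives 1 + 3 + 1 = 5. The article does not say which count applies, so both are shown.

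**3. Error rate if any one score could carry the claim.** This rule is an assumption. Each score is taken as tested at two-sided 5%.

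- One score (PANSS sentence alone): 5%.
- Three independent scores: 1 − 0.95³ = 14.3%.
- Five independent scores: 1 − 0.95⁵ = 22.6%.

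Independence is unrealistic, since all the scores concern positive symptoms and the three subscales share 18 items. The article gives no correlations, so a range was simulated (500,000 draws each, equal correlation between test statistics):

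| Assumed correlation | Three scores | Five scores |
|---|---|---|
| 0.3 | 13.6% | 21.0% |
| 0.5 | 12.5% | 18.2% |
| 0.7 | 10.8% | 14.8% |
| 0.9 | 8.3% | 10.1% |

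With 0.4 between instruments and 0.8 among the Paranoia Checklist subscales, five scores give 17.1%. About 8.6% is the chance of at least one false positive favouring the intervention, against 2.5% for one test.

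**4. What would it cost to keep several primaries?** Same power formula, with Bonferroni α = 0.05/k and any one score sufficient:

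- k = 3 (α = 0.0167): power per score at N = 128 is 65.6%; 80% needs 171, or 190 with 10% attrition.
- k = 5 (α = 0.01): power per score is 58.5%; 80% needs 191, or 213 with 10% attrition.

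A single primary keeps 128 and 80.1%.

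**The case against.** The strongest reply is that the article already has one primary outcome. The only sentence that designates a specific score is the one in the PANSS subsection, and it is unambiguous. The abstract, the Measures section and the Statistical analyses section all speak in the singular, the time point is given as post assessment, and the sample size is for one comparison. On this view the Table 2 grouping is loose labelling, and the MINI's presence there points to a grouping slip rather than a hidden confirmatory test.

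Much of this stands, and it rules out several stronger readings that a reader might infer:

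- **That success on any one of the four suffices.** No sentence says so.
- **That all four are tested at an unadjusted 5%.** The level is stated once, in general. Of the three instruments other than the PANSS, only the LSHS-R has a stated between-group comparison. Rules for multiplicity may properly sit in an analysis plan, so their absence is not itself a fault.
- **That there are at least five primary scores.** The subscales are not declared separate endpoints.
- **That the MINI psychosis diagnosis cannot remit, and so could never show change.** Eligibility uses lifetime criteria, but the article does not say what time frame applies when the MINI is repeated at t2 and t3.

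It is also true that participants' knowledge of allocation comes with any waiting-list design and is not an error in the document. It is a reason for ranking the measures.

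The reply does not remove the conflict. The same article directs readers to Table 2 for its primary measures, and Table 2 lists four.

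**Conclusion.** The point holds as an internal contradiction about the primary outcome: one score in the PANSS subsection, four instruments in Table 2 and the section heading, and nothing in the analysis section to decide between them. It should be corrected before results by group are seen, because the choice cannot credibly be made afterwards.

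The inflation is conditional. If the PANSS sentence governs, the type I error for the primary claim is 5%, so it would be wrong to say flatly that the trial's error rate is inflated. If the Table 2 list governs and any one score may carry the claim, the rate is 14.3% for three independent scores, 22.6% for five, and about 15% to 18% for five at correlations of 0.7 to 0.5. The any-one rule, the number of scores and the correlations are all assumptions. The rate exceeded 5% in every multi-score case examined. The sample size is not in error, and it supports the single-outcome reading.

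**What to change.** State in Measures and in Statistical analyses that the sole primary outcome is the PANSS positive symptom factor at t2 (week 8), tested at two-sided 5%, and that efficacy is concluded only from it. In Table 2 and the section headings, move the Paranoia Checklist and the LSHS-R to the secondary outcomes and class the MINI as an eligibility and descriptive measure.

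The cost is relabelling. Assessments, procedures and the targets of 128 and 140 stay as they are. The one real loss is that a positive self-report result on its own could no longer support the efficacy claim; it would be reported as secondary.
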